**Methods:**

This is a 2-year, prospective, randomized, 2-armed, parallel-group, single-center trial in a German kidney transplant center. All patients will receive the same routine post–kidney transplant care that usually includes follow-up visits every 3 months at the kidney transplant center. For patients in the intervention arm, physicians will be assisted by a validated and previously published AI-based risk prediction system that estimates the risk for graft loss in the next year, starting from 3 months after randomization until 24 months after randomization. The study population will consist of 122 kidney transplant recipients >12 months after transplantation, who are at least 18 years of age, are able to communicate in German, and have an estimated glomerular filtration rate <30 mL/min/1.73 m^2^. Patients with multi-organ transplantation, or who are not able to communicate in German, as well as underage patients, cannot participate. For the primary end point, the proportion of patients who have had a conversation about their treatment options after graft loss is compared at 12 months after randomization. Additionally, 2 different assessment tools for SDM, the CollaboRATE mean score and the Control Preference Scale, are compared between the 2 groups at 12 months and 24 months after randomization. Furthermore, recordings of patient-physician conversations, as well as semistructured interviews with patients, support persons, and physicians, are performed to support the quantitative results.

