### Participants

Participants may enter the trial if all the following apply: (1) they provide written informed consent, (2) they are patients with a functioning kidney allograft, (3) it has been at least 12 months after kidney transplantation, (4) they have an eGFR <30 mL/min/1.73 m^2^ according to Chronic Kidney Disease Epidemiology Collaboration (CKD-EPI) 2021 formula, (5) they are aged at least 18 years, (6) they can communicate in German, and (7) they attend regular follow-ups at KTC. Participants may not enter the trial if any of the following apply: (1) they have undergone multi-organ transplantation, (2) it has been less than 12 months after kidney transplantation, (3) they have an eGFR >30 mL/min/1.73 m^2^ according to CKD-EPI 2021 formula, (4) they are aged less than 18 years, (5) they cannot communicate in German, (6) they do not attend regular follow-ups at KTC, and (7) they enrolled in another interventional study less than 1 month before participation in this study. Additionally, support persons will be eligible if they are nominated by the patient as someone helping them cope with the consequences of their kidney transplant through support, encouragement, and communication. Support persons will be aged 18 years or older, German-speaking, and able to provide informed consent. Treating physicians who work at the participating clinics and use the AI-based decision-support system (DSS) will be eligible to participate in the study. Clinic staff will record the age and gender of nonconsenters who provided permission, which allows for the examination of consent bias.

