### Sample Size

The primary analysis will be performed based on the frequency of conversations about treatment options after graft loss as perceived by the patient, which is assessed in a questionnaire after the respective consultation. Based on the data from Bissonnette et al [10], we estimate that in the control group, 10%-15% of patients will have a conversation about therapy options at the end of graft function. Regarding the intervention studied herein, we estimate that this frequency can be increased to 40%-45%, which is half of the effect size achieved by Bissonnette et al [10]. Using a 2-sided *χ*^2^ test, an α error of .05, and a power of 80%, 25-49 patients per group are needed. Estimating a dropout rate of 10% per year, this increases to 31-61 patients per group. Therefore, 61 patients per group were regarded as sufficient. In order to identify 122 participating patients, local study personnel will have to screen approximately 150 potentially eligible kidney transplant recipients over a period of 6 months.

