#### Intervention Group: AI-Supported Care

The kidney transplant recipients, who are randomized to the interventional arm, will receive identical routine posttransplant care as patients in the control group (see Table 1). In addition, the physicians in the KTC will be provided an AI-based decision support system making predictions for the risk of graft loss based on the patient’s most recent clinical, laboratory, and histopathology data, beginning from the second visit. A previous version of the AI-based decision support system has been studied in silico and in a reader study [11]. The physicians are provided a recommendation on how to proceed in case of a high-risk score. Briefly, physicians are recommended to inform the patients about this risk and discuss the potential necessity of return to dialysis or retransplantation, as well as planning, which mode of renal replacement therapy is preferred by the patient (hemodialysis, peritoneal dialysis, or listing for retransplantation by living donation). Depending on the patient’s preference, preparation for a smooth transition to dialysis or retransplantation should be performed.

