### Outcomes

#### Primary End Points

For the primary end point, the frequency of conversations about treatment options after graft loss as perceived by the patient will be compared between the 2 groups at 12 months after randomization.

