However, if the AI-DSS shows a high risk for graft loss, the physicians are free to discuss this with the patient and offer 1 procedure depending on their own assessment. First, physician—high risk for graft loss: if the physician agrees that there is a high risk of graft loss in a patient during the next year, the physician is advised to discuss this risk with the patient, when the situation is appropriate (enough time, no other major problems to be discussed, etc) or to discuss it during the next appointment. The physician should assess, whether the preferred renal replacement modality (hemodialysis, peritoneal dialysis, and retransplantation) of the patient is known and take measures to ensure a smooth transition without the need for emergency hospitalization (shunt planning, peritoneal dialysis catheter implantation, appointment for living donation, etc). Second, physician—low risk for graft loss: if the physician disagrees with the AI system and estimates a low risk for graft loss in a particular patient, the physician is advised to reconsider potential risk factors. The physician is free to incorporate or ignore the AI-DSS assessment into the SDM with patients and support persons.

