### Statistical Analysis

Preliminary analysis will involve computing descriptive statistics for all quantitative variables. For continuous variables, means, SDs, and quartiles will be estimated, while categorical variables will be summarized with counts and percentages in each category. Summaries will be performed by group and by assessment, as well as for the entire study group. Primary data analysis of the primary end point will involve comparing the frequencies of conversations about treatment options after graft loss between both groups using a 2-sided *χ*^2^ test. Secondary data analysis will include a comparison in secondary outcomes between both groups using a *χ*^2^ test. In general, test results will be described as significant if their *P* values are less than .05 without adjustments for multiple inferences. Multiple imputations will be used to deal with missing data.

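### The primary end point does not require the conversation to precede graft loss, so conversations prompted by graft loss can count as successes and dilute the difference between arms

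*Protocol article*

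**What the plan says.** The end point is described in three places in the protocol article.

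- **Primary End Points:** "the frequency of conversations about treatment options after graft loss as perceived by the patient will be compared between the 2 groups", at 12 months.
- **Abstract, Methods:** "the proportion of patients who have had a conversation about their treatment options after graft loss is compared at 12 months after randomization". This makes it a cumulative yes/no per patient.
- **Sample Size:** the patient's perception, "which is assessed in a questionnaire after the respective consultation".

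None of the three says that the conversation must precede graft loss.

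The purpose is anticipatory. The section on AI-supported care advises physicians, on a high score, to "discuss the potential necessity of return to dialysis or retransplantation". The section on recommended procedures asks them to "take measures to ensure a smooth transition without the need for emergency hospitalization".

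Graft loss is an event after randomization, because of the entry criterion "they are patients with a functioning kidney allograft", with eGFR below 30. It is expected inside the primary window: Textbox 1 lists kidney replacement therapy and emergency dialysis after graft loss at 12 months as secondary end points. Table 2 records graft loss and death at every study visit.

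The only missing-data rule, under Statistical Analysis, is one unqualified sentence: "Multiple imputations will be used to deal with missing data".

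**The concern.** Take a control patient with no earlier discussion who loses the graft at month 8, starts emergency dialysis and is then told the options. If a questionnaire captures that discussion, the patient is a success on the primary end point and also counts under emergency dialysis among the secondary end points. The late conversation that the intervention is meant to make unnecessary scores the same as a planned one.

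Such conversations can occur in both arms whatever the AI system does. They raise both rates and narrow the gap, so a real gain in early conversations could be missed or understated.

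A smaller point concerns death. A patient who dies before month 12 without a recorded conversation has no 12-month response to recover, and the imputation sentence does not separate this from an unreturned questionnaire.

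**Working it through.** **Inputs.** From Sample Size: control rate 10%–15%, intervention rate 40%–45%, two-sided χ² test, α = 0.05, power 80%, dropout 10% per year, 61 per group. The graft-loss share g is my assumption, since the article gives none.

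**The plan's own figure.** n per group = [1.96·√(2p̄(1−p̄)) + 0.8416·√(p₁(1−p₁)+p₂(1−p₂))]² / (p₂−p₁)², with p̄ the mean of p₁ and p₂.

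- 15% vs 40%: (1.96×0.6315 + 0.8416×0.6062)² / 0.0625 = 48.9, so 49.
- 10% vs 45%: (1.96×0.6315 + 0.8416×0.5809)² / 0.1225 = 24.3, so 25.
- Two years of dropout: 49/0.81 = 60.5, so 61; 25/0.81 = 30.9, so 31.

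The stated 25–49 and 31–61 reproduce exactly. The pair 15% vs 40% sets the planned 61.

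**Patients at month 12.** 61 × 0.90 = 54.9, so 55 per arm.

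**Dilution.** Suppose a share g of each arm loses the graft by month 12, independently of any earlier conversation, and all of them report one. Each rate p becomes g + (1−g)p, so the difference becomes (1−g)(p₂−p₁).

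Power = Φ{[(p₂−p₁)√n − 1.96·√(2p̄(1−p̄))] / √(p₁(1−p₁)+p₂(1−p₂))}.

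Example, 15% vs 40% with g = 15% and n = 55:

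- The rates become 27.75% and 49%, a difference of 21.25 points.
- (1.5759 − 1.96×0.6877)/0.6711 = 0.340, so power is 63%.

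Power (%) at 55 per arm:

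| Planning pair | g = 0 | 5% | 10% | 15% | 20% |
|---|---|---|---|---|---|
| 15% vs 40% | 84.5 | 78 | 70 | 63 | 57 |
| 15% vs 45% | 94 | 90 | 84 | 79 | 72 |
| 10% vs 40% | 96 | 92 | 87 | 80 | 74 |
| 10% vs 45% | 99 | 97 | 95 | 91 | 86 |

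With all 61 per arm retained, 15% vs 40% gives 88% at g = 0, then 82%, 75%, 68% and 61%.

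**If only half report a conversation.** The effective share is g/2. At g = 10% the rates are 19.25% vs 43%, and power at 55 per arm is 78% instead of 70%.

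**Deaths.** Suppose a share d of each arm dies without a conversation. If imputation reproduces the arm rates, the 25-point difference (15% vs 40%) stays at 25. If these patients count as no conversation, it is (1−d)×25: 24.5 points at d = 2%, 23.75 at 5% and 22.5 at 10%. These values of d are also assumed.

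**The case against.** The strongest reply is that the article is silent here and lays down no rule. It does not state that conversations after graft loss count, and a condensed article may leave the handling of graft loss and death to a fuller document. For death this largely stands: the imputation sentence does not class an outcome after death as missing. For graft loss it is weaker. Whether a later conversation counts is part of what the primary end point is, and the article defines that end point three times without the restriction.

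The size is also open to challenge, and much of that stands:

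- The graft-loss rate is assumed.
- That every affected patient reports a conversation is a worst case. The questionnaire is tied to a consultation, and nothing shows that a talk during an emergency admission is captured.
- The planning rates are given for all patients in each group. If they already include conversations after graft loss, adding g on top counts these twice.
- 15% vs 40% is the least favourable pair, as the table shows.

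Independence can err the other way. The advice to talk is triggered by high predicted risk, so the AI effect may concentrate in patients who go on to lose the graft. In them, counting later conversations removes the contrast.

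A reader might infer three stronger things that the article does not support.

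- *That the end point no longer measures anticipatory conversations.* It still does in patients who keep their graft and for conversations held before loss. At g = 15%, 85% of the contrast remains.
- *That the plan imputes outcomes for patients who die.* It does not say so.
- *That imputation overwrites a recorded 'yes' after dropout.* A recorded 'yes' is not missing, so the rule does not reach it.

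**Conclusion.** The point holds as a gap in the definition of the primary end point. As worded, a conversation prompted by graft loss counts, which is at odds with the purpose of the intervention and pulls the arms together. Under independence and full reporting the difference shrinks by exactly (1−g). For assumed g of 5% to 20% this costs about 7 to 28 percentage points of power at 55 per arm for the pair that sets the sample size, and about 2 to 13 points for the most favourable pair. The real loss could be smaller or larger, for the reasons given above. The death point is a matter of wording: at most 2.5 points of difference even at an assumed 10% deaths. The clarification should be made, but the gap does not invalidate the design.

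**What to change.** 1. In Primary End Points, and likewise in the abstract and Sample Size, define a success as a conversation reported by the patient before graft loss and by month 12. Graft loss without an earlier reported conversation then counts as 'no'.
2. Keep the unrestricted count as a sensitivity analysis.
3. Limit the imputation sentence to patients whose outcome exists but was not observed. Say how death without an earlier reported conversation is scored. Counting it as 'no' matches the rule for graft loss, though other choices are defensible.
4. State whether the planning rates refer to conversations before graft loss. If they include later ones, the restricted rates will be lower and the sample size should be checked again.

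The cost is wording. The questionnaire follows the consultation, Table 2 has graft loss and death at every visit, and the Safety section requires an onset date for adverse events. Table 2 does not itself list dates, so the record form should capture the date of graft loss explicitly. The downside is small: conversations first held after graft loss drop out of the main analysis. The article reports 19 participants enrolled on March 10, 2024, after ethics approval on August 08, 2023, so nobody enrolled after approval had then reached month 12. Because the trial is open-label, the change should be dated and made before any comparison by arm.

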### Qualitative Research Analysis

Interviews will be transcribed verbatim. The interviews will be recorded for the purpose of transcription on provided devices and will be deleted after the end of the research process. Transcripts will be checked for accuracy by 1 researcher and analyzed using framework analysis. This approach belongs to a broad family of qualitative data analysis methods often related to as “thematic analysis” or “qualitative content analysis” [44]. As suggested by these approaches, both manifest and latent content will be analyzed and descriptive and explanatory conclusions will be drawn from the data [45]. Each interview will serve as a unit of analysis. A journal of reasoning and additional ideas regarding data analysis will help ensure transparency in the coding process. This strategy has been extensively used to facilitate the reconstruction of the analysis and provide justification for the analytical steps undertaken [46,47]. Codes will frequently be compared with each other and parts of the material will be recoded, if necessary, as an intercoder agreement test and additional measure for reliability [48]. This method of qualitative data analysis will provide a systematic model for mapping and interpreting the data and is thus considered appropriate to develop a profound in-depth understanding of participants’ communication experiences and preferences [46,49].

### Data Management

Designated investigator staff must enter the information required by the protocol into the assigned database. Individual interviews, telephone interviews, and patient-physician conversations will be audio recorded, transcribed verbatim by a professional transcriptionist or a research team member, deidentified, and filed for data management and analysis. All qualitative data will be collected by a research team member with extensive experience in qualitative research.

### Safety

Safety assessments will consist of monitoring and recording all adverse events (AEs) and serious AEs, the regular monitoring of blood chemistry and urine, and regular monitoring of vital signs, physical condition, and body weight. Appropriate sponsor personnel and investigators will monitor the safety of the participants throughout the conduct of the study. AEs mean “any untoward occurrence in a trial subject administered an investigational medicinal product and which does not necessarily have a causal relationship with this treatment” [50]. In the PRIMA-AI trial, subjects will not receive any investigational medicinal product, but physicians will be assisted by an AI-based decision support system. Thus, in this study, an AE can be any unfavorable and unintended sign, symptom, or disease (including concomitant illness), deterioration of a preexisting illness, accident, any suspected drug reaction, or a clinically relevant change of laboratory values whether or not considered to be related to the AI-based intervention. Adverse reactions (ARs) mean “all untoward and unintended responses to an investigational medicinal product unrelated to the dose administered” [50]. In PRIMA-AI, subjects will not receive any investigational medicinal product. Therefore, the definition of AR implies in this trial a reasonable possibility of a causal relationship between the event and the investigational AI-based intervention.

The period of observation for AEs extends from the baseline visit (month 0, visit 1) after informed consent was given until and including month 24 (visit 5). AEs have to be followed up until resolution or stabilization or until the subject’s end-of-study visit (month 24, visit 5), whichever comes first. Preexisting conditions that do not worsen during the course of the study are not reportable as AE. To determine whether a condition has worsened, it is compared to the condition of the subject at baseline visit (month 0, visit 1). All AEs, whether volunteered by the patient, discovered by investigator questioning, or detected through physical examination, laboratory test, or other means will be assessed and recorded in detail in the subject’s file and on the case report form, the AE report form. All AEs will be coded appropriately at the end of the clinical study using MeDRA or, in addition, on request by the study coordinator.

The following information must be recorded: (1) AE diagnosis (if possible) or main symptom; (2) date (and time, if relevant) of onset; (3) severity (maximum observed); (4) causal relationship (reasonable possibility or no reasonable possibility); (5) seriousness (yes or no); (6) outcome; (7) action taken with the study intervention; (8) AE leading to discontinuation of the study subject (yes or no); (9) treatment of AE; and (10) stop date (and time, if relevant). For the assessment of severity, the investigator should use grades from 1 to 5 as outlined in Textbox 2.

Grades of assessments of severity for adverse events.
**Grade 1**
Mild or asymptomatic symptoms, clinical or diagnostic observations only, and intervention not indicated.
**Grade 2**
Moderate, minimal, local, or noninvasive intervention indicated, and limiting age-appropriate instrumental activities of daily living. Instrumental activities of daily living are activities such as preparing meals, shopping for groceries or clothes, using the telephone, managing money.
**Grade 3**
Severe or medically significant but not immediately life-threatening, hospitalization or prolongation of hospitalization indicated, disabling, and limiting self-care activities of daily living. Self-care activities of daily living are activities such as bathing, dressing and undressing, feeding oneself, using the toilet, taking medications, and not being bedridden.
**Grade 4**
Life-threatening consequences and urgent intervention indicated.
**Grade 5**
Death related to adverse event.

### Ethical Considerations

Written informed consent will be collected from all study participants before performing any research activity by a research team member. To ensure the eligibility of a participate in the trial, the researcher will review the inclusion and exclusion criteria with potential participants prior to beginning the informed consent process. Prospective participants will be asked to personally sign and date the latest approved version of the informed consent forms before any trial procedure is performed. During the informed consent process, study participants will be informed of their right to withdraw from the study at any time without any impact on their treatment at the KTC. This study will be conducted in accordance with the tenets of the Declaration of Helsinki (1996). The ethics committee of Charité—Universitätsmedizin Berlin approved this study (EA1/177/23; August 08, 2023).

The trial results will be disseminated through a variety of strategies, including academic publications, research reports, infographics, media releases, and community events. Trial participants’ anonymity and confidentiality will be protected during these activities by removing all identifiable information from the knowledge dissemination products.

## Results

As of March 10, 2024, we enrolled 19 participants. The first results are expected to be submitted for publication in 2025.

## Discussion

### Principal Findings

This study is designed to investigate the influence of AI-based risk prediction on the frequency of conversations about treatment options after graft loss and the associated SDM process with a randomized design using a mixed methods approach. It is the first study in the context of kidney transplantation to analyze the potential effects of AI-based interventions on physician-patient interaction.

Despite tremendous enthusiasm surrounding the potential for AI to improve medical prognosis, diagnosis, and decision-making, only limited empirical data are available to help understand patients’ and physicians’ perspectives on how AI impacts their interactions, specifically SDM [16]. In the context of kidney transplantation, AI research has mostly focused on technical and medical challenges relating to robustness and implementation, excluding the sociotechnical environment into which such systems are embedded [12-14]. In the treatment of patients with cancer, an intervention that delivered machine learning mortality predictions with behavioral nudges to oncology clinicians significantly increased the rate of serious illness conversations [51,52]. While serious illness conversations are only in part comparable to conversations about graft loss, returning to dialysis after transplantation is also a life-changing event with serious effects on quality of life. We argue that increasing the frequency of conversation about treatment options after graft loss and improving SDM may improve patient satisfaction comparable to patients with chronic kidney disease without transplantation [6].

